## Abstract

**Background:**

Provision of anticipatory guidance for parents is recommended as an effective strategy to prevent injuries among young children. Technology-based anticipatory guidance has been suggested to reinforce the effectiveness of injury prevention and improve parents’ knowledge of child safety.

**Objective:**

This study aims to examine the effectiveness of a technology-based injury prevention program with parental anticipatory guidance for enhancing mothers’ knowledge of child safety.

**Methods:**

In this randomized controlled trial, 308 mothers will be recruited from the antenatal clinics and postnatal wards of two major public hospitals in Hong Kong. Participating mothers will be randomly assigned into intervention and control groups. Mothers in the intervention group will be given free access to a technology-based injury prevention program with anticipatory guidance, whereas mothers in the control group will be given a relevant booklet on parenting. The injury prevention program, available as a website or on a mobile app, includes behavioral components based on the Theory of Planned Behavior. The primary outcome measure will be the change in the mother’s knowledge of child safety. The secondary outcome measures will be age-appropriate domestic safety knowledge, attitudes, intentions, perceived behavioral control, and self-reported behavior related to home safety practice. We will also determine dose-response relationships between the outcome measures and the website and mobile app usage.

**Results:**

Enrolment of participants will begin in October 2016. Results are expected by June 2018.

**Conclusions:**

Parents will be able to easily access the domestic injury prevention website to find information regarding child injury prevention. It is anticipated that the technology-based intervention will help parents improve their knowledge of child safety and raise their awareness about the consequences of domestic injuries and the importance of prevention.

**Trial Registration:**

Clinicaltrials.gov

Clinicaltrials.gov NCT02835768; http://clinicaltrials.gov/ct2/show/NCT02835768 (Archived by WebCite at http://www.webcitation/6lbXYM6b9)

## Introduction

Childhood injury is a major public health problem worldwide [1]. According to the World Health Organization, approximately 46 out of every 100,000 children under the age of 5 years die from unintentional injuries [2]. Childhood injury is a significant health problem in Hong Kong. Between 2010 and 2012, more than 740,000 injury cases were reported in children aged 0 to 19 attending Accident and Emergency Departments in Hong Kong [3]. Specifically, pediatric unintentional domestic injury was one of the top three injury types among children in Hong Kong, accounting for 38.67% (286,193/740,000) of injuries in the 0 to 19 age group [3]. In the 0 to 4 age group, domestic injury was the leading cause of injury, accounting for 64% of all injuries. Unlike intentional injury caused by domestic violence, pediatric unintentional domestic injury is associated with the lack of available living space and safety measures, parents’ poor perception of injury risk, and children’s injury risk behaviors.

Parents are the primary caregivers and role models for their children’s behavior, and they should be given guidance regarding domestic injury prevention and how to modify the home to be a safe environment [4,5]. Although health care professionals are perceived as a credible provider of injury prevention information [6,7], parents will need to play an influential role in reducing their children’s exposure to injury risk by adopting better childcare practices and using appropriate child safety devices in the home [8,9]. Anticipatory guidance provided to parents during pediatric medical care is an effective strategy to prevent injuries and promote child health [10]. Anticipatory guidance consists of useful information for parents and families about their children’s development, and practical information on how to promote this development and adopt good practices [11]. Anticipatory guidance can be delivered in line with developmental milestones of a child [12]. Previous studies on the effectiveness of anticipatory guidance indicated that parent and child behavior outcomes were associated with reduced injuries and improved development during infancy and early childhood [7,13,14].

Technology-based interventions with anticipatory guidance information can be accessed anonymously, anytime, and anywhere. These systems can provide individualized and tailored interfaces enriched with interactive elements [15], and such interventions could be a useful approach for the prevention of domestic injury. Recent studies suggest that technology-based interventions can reinforce the effectiveness of injury prevention, and improve parents’ knowledge of child safety [16-18]. A systematic review of technology-based interventions for unintentional injury prevention highlighted 10 parenting interventions for child safety; all interventions were demonstrated to improve parents’ injury prevention behaviors [19]. For instance, a study by Van Beelen et al revealed that a Web-based intervention increased parents’ behavior toward child safety more than a standard leaflet related to scheduled childcare counseling [20]. Only two interventions evaluated changes in safety knowledge, and both showed positive changes [19]. A study by Gielen et al reported that an online intervention had a positive effect on enhancing safety knowledge [21]. Furthermore, the systematic review found only two out of 44 technology-based interventions were available as mobile apps [19]. Mobile apps for injury prevention intervention should be developed and thoroughly evaluated.

In this study, we propose to develop a new technology-based intervention that includes parental anticipatory guidance related to child injury prevention that is accessible on the web and as a mobile app. We will examine the effectiveness of the intervention in enhancing mothers’ knowledge of child safety. Using our new technology-based approach, we aim to motivate mothers to learn about pediatric unintentional domestic injury prevention to improve their knowledge of child safety, attitudes, and perceived behavioral control toward home safety practice. Website usage will be evaluated in terms of its reach and engagement statistics. User acceptance evaluations will be conducted at the end of the intervention period to collect feedback on the website interface.

## Methods

### Study Design

This study will be a randomized controlled trial of the effectiveness of a technology-based injury prevention program for enhancing mothers’ knowledge of child safety (Figure 1). Mothers will be recruited from the antenatal clinics and postnatal wards of two major public hospitals in Hong Kong: Kwong Wah Hospital and Queen Mary Hospital. Between October, 2016 and January, 2017, nurses will identify potential participants. An experienced research assistant will provide the participants with an information sheet explaining the study, along with a consent form. The inclusion criteria will include mothers attending the antenatal clinics or staying in the postnatal wards at Kwong Wah Hospital or Queen Mary Hospital. The exclusion criteria will include subjects unable to read Chinese, and those without Internet access.

Participants will be randomly allocated into the intervention and control groups in a 1:1 ratio. All participants will be given an information pack consisting of a parenting booklet from the Maternal and Child Health Centers (MCHC). This booklet is publicly available and provides brief and general home safety tips for mothers with children under 3 years of age. The intervention group will also be given an additional leaflet containing a brief introduction to the Internet-based domestic safety platform, and instructions on how to access the website. Mothers can easily access this practical online parenting resource through the website or a mobile app. The online resource contains information on various safety topics and educational materials, including general and age-appropriate injury prevention measures suitable for mothers with infants and children between 2 and 18 months of age. Participants in the intervention group will be periodically contacted by telephone and electronic messaging to encourage them to access and engage with the domestic safety website. The research team will provide technical support to all participants who encounter problems accessing the intervention website or mobile app. Apart from technical support, no other intervention will be provided to those accessing the website or mobile app by any therapist, nurse, care provider, or physician. The control group will receive only the MCHC parenting booklet.

All consenting participants will be asked to complete a general safety questionnaire at the antenatal clinic or postnatal ward of the two hospitals. Age-appropriate safety knowledge, attitudes, intentions, perceived behavioral control, and self-reported behavior related to home safety practice will be assessed at specific child developmental ages at 2, 6, 9, 12, and 18 months. Participants in the intervention group will be given immediate feedback on their specific injury prevention behaviors prompted by the *at-risk* (incorrect) answers obtained from their completed questionnaire. This online feedback counseling approach aims to educate mothers and enhance their awareness related to domestic injury prevention. At the end of the counseling session, each intervention participant will be provided with age-appropriate safety information. Participants’ general safety knowledge will be reassessed when their children reach the age of 18 months. Intervention participants will be reminded by telephone and email to complete the age-appropriate safety questionnaires at each developmental stage, and the final general safety questionnaire. Control group participants will be contacted using the same schedule, to remind them to read the booklet and to complete the questionnaires.

This study is registered with Clinicaltrials.gov (Identifier: NCT02835768) and has been approved by the Institutional Review Board of Hong Kong University and Hospital Authority Hong Kong West Cluster (Reference number: UW 15-465). All participants will provide written informed consent.

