### Randomization and Masking

Participants will be randomly assigned to the intervention group or the control group by stratified randomization within each hospital, using random numbers generated using R Statistical Software. Each participant will receive a sealed opaque envelope assigning them to either the intervention (website and mobile app access) or the control (no website or mobile app access) groups. The participant recruitment and randomization process will be independently carried out by different research assistants. Outcome assessors will be blinded to the allocation of participants in each group.

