### Data Analysis

Changes in participants’ knowledge of child safety will be studied by comparing their knowledge before and after completing the injury prevention program, and by comparing the participants’ knowledge of child safety in the intervention and control groups. Regression analysis will be used to examine the intervention effectiveness, adjusted for participant demographics (eg, gender, age, and socioeconomic status of the parent). Data will be analyzed by an intent-to-treat approach to address loss of any follow-up data. Independent sample t-tests will be used to examine the between-group differences in age-appropriate safety knowledge, attitudes, intentions, perceived behavioral control, and actual behavior related to home safety practice. Dose-response relationships between the outcome measures and the website and mobile app usage will be determined by correlation analysis. Website and mobile app usage data will be summarized based on the number of users and their time spent using these resources during the entire intervention period. A summary of the user acceptance evaluation will be compiled to improve and develop the website and mobile app.

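### Baseline is taken before birth in some women and after birth in others, but recruitment setting is neither a stratum nor a named covariate, and length of access is mixed into the usage dose

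*Protocol article*

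**What the plan says.** Under Study Design, eligibility is defined by place: "The inclusion criteria will include mothers attending the antenatal clinics or staying in the postnatal wards at Kwong Wah Hospital or Queen Mary Hospital". The two exclusions concern literacy and connectivity: "The exclusion criteria will include subjects unable to read Chinese, and those without Internet access". Baseline is measured where the woman is recruited: "All consenting participants will be asked to complete a general safety questionnaire at the antenatal clinic or postnatal ward of the two hospitals". The other end of the primary change score is set by the child's age: "general safety knowledge will be reassessed when their children reach the age of 18 months". The secondary assessments are also tied to child age (2, 6, 9, 12 and 18 months).

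Randomization and Masking names one stratification factor: "Participants will be randomly assigned to the intervention group or the control group by stratified randomization within each hospital".

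Data Analysis adjusts the effectiveness regression for participant demographics, with gender, age and socioeconomic status as examples. It determines dose-response by correlating outcomes with website and app usage. Of usage it says "Website and mobile app usage data will be summarized based on the number of users and their time spent using these resources during the entire" span of the intervention. The article does not say when that period begins for a woman recruited before birth. Study Design describes the access leaflet as part of what the intervention group receives on allocation.

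**The concern.** The primary outcome is a change between two assessments. The first is set by the date of recruitment and the second by the date of birth, so the time between them depends on where, and how late in pregnancy, the woman was recruited. Baseline knowledge is also measured before birth in one setting and after birth in the other.

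Two things are at stake. First, a factor that is known at enrolment and may predict knowledge or its change is left out of both the stratification and the named covariates. This gives up some precision and allows chance imbalance between arms. Second, usage totals exist only in the intervention arm. A woman with more months of access can log more use for that reason alone, so a correlation between total use and outcome partly reflects recruitment timing.

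**Working it through.** **The plan's own figures.** The Sample Size section gives d = 0.42, 80% power, 5% significance, 92 subjects and 154 recruited per group. Two-sided normal approximation: 2 × (1.96 + 0.842)² / 0.42² = 89 per group; the t-test version gives 90, close to the stated 92. Attrition: 92 / (1 − 0.40) = 153.3, so 154 per group and 308 in total. These figures reproduce and are not in dispute.

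**Baseline-to-endpoint interval.** Assumptions not in the article: birth at 40 weeks, antenatal entry between 12 and 36 weeks, 30.44 days per month. Interval = 18 + (40 − week at entry) × 7 / 30.44 months.

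| Recruited | Extra months | Interval (months) | Ratio to 18 |
|---|---|---|---|
| Postnatal ward | 0 | 18.0 | 1.00 |
| Week 36 | 0.9 | 18.9 | 1.05 |
| Week 28 | 2.8 | 20.8 | 1.16 |
| Week 20 | 4.6 | 22.6 | 1.26 |
| Week 12 | 6.4 | 24.4 | 1.36 |

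This needs only the stated place of baseline and the stated endpoint. It does not depend on when the allocation envelope is opened.

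**Chance imbalance in setting.** Assume half of each arm is recruited antenatally; the article gives no split.
- With 154 per arm, the SD of the between-arm difference in antenatal share is √(0.25 × 2 / 154) = 0.057. The 95% range is ±1.96 × 0.057, about ±11 percentage points.
- With 92 evaluable per arm, the SD is √(0.25 × 2 / 92) = 0.074, and the range about ±14 points.

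**What that could do to the primary comparison.** The article gives no association between setting and knowledge change. As an illustration only, let the two settings differ by as much as the planned effect, 0.42 SD.
- An imbalance at the 95% limit among evaluable women shifts the between-arm difference by 0.145 × 0.42 = 0.06 SD.
- Setting then explains 0.5 × 0.5 × 0.42² = 0.044 of the outcome variance. Adjusting for it is worth about 4% in sample size, or 92 × 0.044 ≈ 4 women per group. With no association, nothing is gained.

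**What it does to the usage dose.** Take two intervention mothers with the same monthly use, u, and access from enrolment to child age 18 months. The postnatal recruit logs 18u and the week-12 recruit 24.4u: the same behaviour, with a recorded dose 36% higher. Counted from birth, both log 18u.

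**The case against.** The strongest reply is that tying outcomes to child age is a sound choice. The trial asks what mothers know when the child is 18 months old, the content follows developmental stage, and a between-arm contrast does not require equal time since baseline. Setting and gestation are independent of arm under randomisation, chance imbalance is already covered by the significance level, and stratifying by hospital alone is acceptable with 308 women. All of this stands. It rules out bias in the primary comparison and leaves a modest question of precision. It does not answer the dose-response point, because usage is not randomised.

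It is also fair that the spread rests partly on silence. A condensed article may omit a gestational window held in the full protocol, and recruitment only near term would shrink the difference to about a month. The covariate list is given as examples, so setting is not ruled out.

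A reader might infer more, which the article does not support:
- **Women are randomised before birth at any gestation.** This is a natural reading for antenatal recruits, but the time of allocation and the gestational range are not stated.
- **Pregnancy or newborn loss undermines the attrition allowance.** The 40% allowance is not limited by cause, and handling of such losses is detail that an article may leave to the full protocol.
- **Women may be enrolled twice, or contacted about a child after a loss.** Nothing in the text says that either would happen.

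**Conclusion.** The point holds as a cheap improvement to the design and analysis. The baseline-to-endpoint interval differs by recruitment setting: 18 months against roughly 19 to 24 months, assuming entry at 36 to 12 weeks and birth at 40 weeks. Setting is neither a stratum nor a named covariate.

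For the primary comparison there is no systematic bias. The cost is avoidable noise and a possible imbalance of about ±11 percentage points in antenatal share at randomisation, assuming a 50:50 mix. Its effect on the estimate is probably small and cannot be fixed from the article, because the association of setting with knowledge change is not given.

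The firmer consequence is for the dose-response analysis. If access starts at enrolment, as Study Design suggests but does not state, total usage carries length of access with it, by up to 36% on the same gestation assumption. If access in fact starts at birth, this part falls away.

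**What to change.** 1. Stratify randomisation by hospital and recruitment setting. This makes four strata, averaging 308 / 4 = 77 women, and both factors are known at enrolment.
2. Name recruitment setting as a covariate in the effectiveness regression.
3. In the dose-response analysis, count usage from the child's birth, or adjust for months of access. Setting alone is not enough here, because access also varies within the antenatal group. Length of access would then no longer be confused with dose, although the correlation would remain observational.

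The cost is two extra strata in the allocation list, one covariate and a date calculation for usage. No extra staff or visits are needed, and the child-age assessment schedule does not change.

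Moving baseline and randomisation to the postnatal ward would equalise the intervals, but it is not recommended because it is not cheap. Assume entry uniform over 12 to 36 weeks and over the 123-day (17.57-week) October to January window, with birth at 40 weeks. The share of antenatal consenters delivering inside the window is then (13.57² / 2) / (24 × 17.57) = 0.22, where 13.57 = 17.57 − 4. About 78% would be lost to randomisation unless the window were extended or ward recruitment made up the shortfall.

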### Sample Size Calculation

With reference to a computer-based parenting intervention for child injury prevention that reported a small to medium effect (d=0.42) for knowledge change [21], 92 subjects will be needed for this intervention study to detect an effect with 80% power and a 5% significance level. Assuming a 40% attrition rate between preevaluation and postevaluation, at least 154 participants should be recruited to each of the intervention and control groups.

### Randomization and Masking

Participants will be randomly assigned to the intervention group or the control group by stratified randomization within each hospital, using random numbers generated using R Statistical Software. Each participant will receive a sealed opaque envelope assigning them to either the intervention (website and mobile app access) or the control (no website or mobile app access) groups. The participant recruitment and randomization process will be independently carried out by different research assistants. Outcome assessors will be blinded to the allocation of participants in each group.

### Technology-Based Anticipatory Guidance

The technology-based intervention website will be developed using the existing injury prevention website designed by the Hong Kong Childhood Injury Prevention and Research Association (CIPRA), which provides informational, educational, and motivational support to parents [22]. The existing CIPRA website contains assorted safety information (not limited to domestic safety) and online games to deliver safety messages. The CIPRA website includes two key topics on (1) types of domestic injury, and (2) preventing a range of domestic injuries. In this study, the technology-based website used by the intervention group will be based on the CIPRA website, but with limited access to only the domestic safety and domestic injury prevention topics. Topics related to domestic injury will be temporarily suspended from the main CIPRA website during the study period. A mobile app will also be developed in conjunction with the website platform to facilitate participants’ acquisition of knowledge regarding child-related domestic injury prevention. The contents of the intervention website and mobile app will be the same.

The Injury Prevention Program (TIPP), an intervention website introduced by the American Academy of Pediatrics [23], will be the basis for the core strategy of our domestic injury prevention intervention. A review of the literature on childhood injury prevention demonstrated that TIPP was effective in improving safety knowledge and home safety practices [24]. Our intervention program will provide anticipatory guidance via the general domestic safety tips from the CIPRA website and TIPP. These combined resources will provide enriched domestic injury prevention information (*Home Safety Tips*) which will be divided into five stages according to the safety issues relevant to infants/young children in various age groups (Table 1). The intervention platform is intended to provide mothers with domestic injury prevention information specific to their children’s age, and important injury prevention information and messages will be age-appropriate for each developmental stage. Mothers will complete a corresponding safety survey at each developmental stage that their children reach. Safety counseling topics include common injury types such as falls, drowning, burns, and poisoning, but not unintentional firearm injury. Firearms, guns, and other weapons are prohibited by law in Hong Kong, so it is unlikely that children will be injured in such a way.

